# Comparative Effectiveness of Different Surgical Timings on Neurological Outcomes for Cranioplasty

# Abstract

## Research Design (Multiple choices allowed)

□ Case-control study
□ Cohort study
□ Cross-sectional study
□ Randomized controlled trial

🗹 non-Randomized controlled trial
□ Blinded
□ Others:

## Total Number of Cases

500

## Risk/Benefit Analysis

Decompressive craniectomy can effectively treat refractory intracranial hypertension that persists despite medical intervention. Postoperatively, the risk of trauma increases due to the absence of a protective skull flap, and the risk of complications such as infection, hydrocephalus, and cerebrospinal fluid leakage also rises. Although studies show that the complication rate after cranioplasty can reach 30%, long-term research indicates that cranioplasty can prevent some complications and aid in neurological recovery and appearance restoration, helping patients return to normal life sooner. Regarding whether the timing of cranioplasty affects the incidence of complications and neurological outcomes, existing evidence presents conflicting views. Despite a recent comprehensive systematic review concluding that early cranioplasty can enhance neurological function, the strength of the supporting evidence is relatively low, including only retrospective and small-scale studies. Therefore, the relationship between the timing of cranioplasty and its outcomes remains controversial.

## Risk Assessment

🗹 Not greater than minimal risk
□ Greater than minimal risk

Minimal risk: The likelihood and magnitude of harm or discomfort anticipated in the research are not greater than those ordinarily encountered in daily life or during the performance of routine physical or psychological examinations.

# I. Research Background

Decompressive craniectomy effectively relieves refractory intracranial hypertension caused by cranial injuries. Secondary cranioplasty is a necessary and common neurosurgical procedure aimed at restoring skull integrity and assisting in the recovery of neurological function. Despite the relative simplicity of cranioplasty, it is associated with a high complication rate (15%-35%). The main issues surrounding cranioplasty include:
1. Management of complications secondary to decompressive craniectomy;
2. Choice of materials for cranioplasty;
3. Interval between decompressive craniectomy and cranioplasty;
4. Management of hydrocephalus following decompressive craniectomy and cranioplasty;
5. Management of temporal muscle atrophy post-cranioplasty.

There are ongoing controversies regarding the choice of materials for cranioplasty, such as traditional autologous bone, titanium, and recent polyetheretherketone materials. The optimal timing for cranioplasty and its impact on postoperative complications is also debated. This study aims to analyze the clinical outcomes of cranioplasty performed at different times and to determine the optimal timing for cranioplasty using a larger sample size to guide clinical treatment.

# II. Research Objectives

## Primary Objectives

1. Analyze the neurological outcomes of cranioplasty performed at different times.

## Secondary Objectives

1. Analyze the incidence of postoperative complications of cranioplasty performed at different times;
2. Establish relevant clinical predictive models.

# III. Research Design Type, Principles, and Sample Sources

## 1. Research Design

### Overall Design

This study is designed as a prospective, multicenter, non-randomized controlled trial to evaluate the outcomes of early versus late cranioplasty in patients following decompressive craniectomy. The trial is organized to compare two distinct patient groups based on the timing of their cranioplasty procedure. The early group will consist of patients receiving cranioplasty within 6 weeks to 3 months post-decompression, while the late group will include those undergoing the procedure later than 3 months post-decompression. The trial will enroll participants from 10 clinical centers across China, selected based on their high standards of care and previous experience with similar studies. As postoperative neurological evaluation is the primary indicator, the main objective is to analyze neurological outcomes of cranioplasty performed at different times. All analyses will be conducted anonymously to protect patient privacy.

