### Sample Size

Recruitment for this study is scheduled to commence in January 2025 and is anticipated to conclude by January 2026. We aim to enroll a minimum of 500 patients who have undergone decompressive craniectomy. The study will run until August 2026, which marks the final follow-up assessments for the last recruited participants.

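### The protocol aims to find the optimal timing of cranioplasty, but the only comparison it fixes is a single cut at 3 months with an open-ended late group, which cannot locate an optimum

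*Protocol*

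**What the plan says.** The aim and the comparison stand in different sections of the protocol.

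- **Aim (I. Research Background):** the study is "to determine the optimal timing for cranioplasty using a larger sample size to guide clinical treatment".
- **Primary objective (II. Research Objectives):** "Analyze the neurological outcomes of cranioplasty performed at different times". This does not say how many timing categories there are.
- **Comparison (III.1 Overall Design):** "The trial is organized to compare two distinct patient groups based on the timing of their cranioplasty procedure". The first of these has a window closed at both ends: "The early group will consist of patients receiving cranioplasty within 6 weeks to 3 months post-decompression". The second has a lower limit of 3 months and no upper limit.
- **Size (III.1 Sample Size):** "We aim to enroll a minimum of 500 patients who have undergone decompressive craniectomy".
- **Methods (IV.3 Data Collection and Management):** stratified, multivariate and propensity-score methods are named, all to deal with bias and confounding. The interval is not named as a continuous exposure, and no third timing category appears anywhere.
- **Source population (III.2):** patients having cranioplasty in the department in 2025 to 2026, with no minimum interval stated.

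**The concern.** To locate an optimum, one must know how the outcome varies along the interval. Two group means give a single difference at a cut chosen beforehand. Many different curves produce the same difference, including curves with quite different peaks and a flat one.

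The open-ended late group adds a second problem. Surgery shortly after 3 months and surgery at 18 months count as the same exposure, so the late mean averages the curve over whatever intervals happen to be enrolled. Two studies following this protocol, with the same true curve but different shares of very late patients, would expect different results.

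The stake is the conclusion, which is meant to guide treatment. A difference in favour of one side could be reported as the optimal timing when it only ranks two averages. A null result could be read as timing not mattering when a clear peak lies just above the cut.

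**Working it through.** The plan gives no figure on this point to reproduce, and no distribution of intervals. The logical step comes first, followed by two illustrations on assumed inputs.

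**1. Aim against comparison.** Let f(x) be the mean outcome at interval x. The fixed contrast estimates D = mean of f(x) over early patients minus mean of f(x) over late patients. D is one number. The position of the maximum of f is a feature of the whole curve and cannot be recovered from D. This holds even before confounding is considered.

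**2. Single-peaked illustration.** Assumptions: interval lognormal, median 4 months, log-SD 0.5, truncated at 6 weeks (taken as 1.4 months); outcome f(x) = -(ln x - ln t)², with optimum t. Then

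D(t) = [E(L² | late) - E(L² | early)] - 2 ln t [E(L | late) - E(L | early)], where L = ln x.

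- Share early: 27%.
- Early: E(L) = 0.8307, E(L²) = 0.7278. Late: E(L) = 1.6219, E(L²) = 2.7573.
- Differences: 1.6219 - 0.8307 = 0.7912 and 2.7573 - 0.7278 = 2.0294.
- D = 0 at ln t = 2.0294 / (2 × 0.7912) = 1.2825, so t = 3.61 months.
- At t = 3: 2.0294 - 2 × 1.0986 × 0.7912 = +0.29.

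Over a range of optima, in units of the curvature:

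| True optimum (months) | 2 | 3 | 3.6 | 4.5 | 5.5 |
|---|---|---|---|---|---|
| Expected early minus late | +0.93 | +0.29 | 0.00 | -0.35 | -0.67 |

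In this example, an optimum at 3.6 months and no effect of timing give the same expected result.

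In a simulation of 500 patients (2,000 runs, curvature 0.5 SD per squared log unit, two-sided 5% level), the two-group test had 5% power at an optimum of 3.6 months, against 93% for a quadratic in log interval. At an optimum of 3 months the figures were 29% and 99%. The quadratic is the true model here, so this comparison favours it.

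**3. Dependence on the late-group mix.** Keep the same curve and early group, but suppose no late patient happens to be operated after 6 months. This is a device to change the mix, not a proposed limit.

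- Late: E(L) = 1.4363, E(L²) = 2.1006. Differences: 0.6056 and 1.3728.
- With the optimum at 3.3 months (ln 3.3 = 1.1939), the open-ended group gives 2.0294 - 2 × 1.1939 × 0.7912 = +0.14.
- The shorter late group gives 1.3728 - 2 × 1.1939 × 0.6056 = -0.07.

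The true curve is unchanged and the sign reverses.

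**4. Information kept for a trend.** Assumption: interval = 1.38 months (6 weeks) + exponential with mean θ months. The share of information kept by the early/late indicator is its squared correlation with ln x:

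r² = p(1 - p)(late mean - early mean)² / variance, with early share p = 1 - exp(-(3 - 1.38)/θ).

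| θ | p | Early mean of ln x | Late mean of ln x | Variance of ln x | r² |
|---|---|---|---|---|---|
| 3 | 0.417 | 0.726 | 1.695 | 0.352 | 0.65 |
| 4 | 0.333 | 0.734 | 1.819 | 0.433 | 0.60 |
| 5 | 0.277 | 0.740 | 1.927 | 0.501 | 0.56 |

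For θ = 3: 0.417 × 0.583 × (0.969)² / 0.352 = 0.65. Under other assumed shapes (uniform or lognormal), the log-linear figure ranges from 55% to 74%.

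**The case against.** The strongest reply is that optimal timing appears only in the Background. The objectives speak of outcomes at different times, and the Overall Design speaks of early versus late, which two groups do answer. That stands in part: the two-group comparison is a legitimate analysis of its own question. But the Background sentence is where the protocol states what the study is for, and the comparison does not deliver it.

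A reader might go on to infer that the protocol throws the interval data away. The document does not support that. No section excludes a continuous analysis, and an analysis plan not seen here, or the predictive models among the secondary objectives, might use the interval. The loss applies to the two-group contrast alone.

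A reader might also turn 56-65% into the equivalent of 175 to 220 of 500 patients lost (500 × 0.35 and 500 × 0.44). That would be true only for a log-linear trend under an assumed distribution, and a monotone trend has no interior optimum. It should not be quoted as the cost of this design.

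Nor can it be said that patients operated before 6 weeks are recruited and then dropped. They fit neither group, and the source-population section sets no minimum interval, but the text at hand does not settle whether they enter the study.

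Finally, an adjusted curve would not prove an optimum either, since in a non-randomised study the interval may track recovery and fitness for surgery. That stands, and it limits how the added model should be worded.

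**Conclusion.** The point holds as a mismatch between the stated aim and the only comparison fixed. Carried out as written, the comparison can rank the two sides of 3 months on average in the enrolled case mix; it cannot determine the optimal timing. This rests on no numerical assumption.

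How misleading the contrast could be depends on the unknown curve and intervals. Under the assumptions shown, the expected difference vanishes for an optimum near 3.6 months, and its sign can turn on the late-group mix alone.

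The two-group analysis remains usable for its own question. The change should be made, but the design is not invalid without it.

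**What to change.** 1. Keep the two-group contrast and word its conclusion as before or after 3 months, not as optimal.
2. Pre-specify, as the analysis for the Background aim, a confounder-adjusted model with the decompression-to-cranioplasty interval in days as a flexible continuous term. A restricted cubic spline is one suitable choice. Report the curve with confidence bands and the distribution of intervals in the late group.
3. Describe the curve as an adjusted association, because the interval is not randomised.
4. If that model is not added, restrict the Background aim to early versus late.
5. Reconcile the Overall Design with section III.2 on whether patients operated before 6 weeks are in the study.

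The cost is one extra model, some wording and a more modest stated conclusion. The interval must be known to assign patients to groups, although the protocol lists no data field for it, so the operation dates should be confirmed on the case report form. No extra patients or visits are needed. Fixing the model in advance also avoids cut-points chosen after the data are seen.

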### Sample Size

Recruitment for this study is scheduled to commence in January 2025 and is anticipated to conclude by January 2026. We aim to enroll a minimum of 500 patients who have undergone decompressive craniectomy. The study will run until August 2026, which marks the final follow-up assessments for the last recruited participants.

## 2. Medical Records / Specimen Names, Sources, Periods, Acquisition, Processing, and Disposal

Patients undergoing cranioplasty in our department from 2025 to 2026 due to various reasons leading to decompressive craniectomy will be prospectively collected and analyzed. All analyses will be conducted anonymously, protecting patient privacy and data confidentiality.

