# IV. Quality Control and Assurance

## 1. Subject Compliance

Patient follow-up management is key to ensuring research quality. A standardized follow-up plan will be developed. Patients will be informed and educated at the start of the study. Follow-up visits will be scheduled at 3 months and 6 months post-cranioplasty until follow-up data collection is completed. The study will terminate once 6-month follow-up data is collected.

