## 3. Data Collection and Management

Follow-up will primarily be conducted in outpatient clinics, with information recorded in case report forms and entered into an electronic data collection database. The electronic database will be developed and maintained by researchers independent of West China Hospital, Sichuan University. Data will be organized and analyzed by personnel with a background in epidemiology. Considering potential biases and confounding factors in real-world research, measures will be taken to include these factors in the research plan and case report forms. Statistical methods such as stratified analysis, multivariate analysis, and propensity score will be used to control and correct these factors during data analysis.

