# V. Ethical Principles and Requirements

This clinical research will adhere to the Declaration of Helsinki and relevant regulations of the National Health and Family Planning Commission of the People's Republic of China. As a prospective observational study, it involves no intervention, only prospective data collection. Personal information of subjects will be anonymized, ensuring no risk to subjects and no adverse effects on their rights and health. Research data will be stored at West China Hospital, Sichuan University. Researchers, regulatory authorities, and the ethics review committee may review the data. Public reports will not disclose the personal identity of subjects. Efforts will be made to protect the privacy and personal information of subjects within the legal scope.

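### Patients enter at cranioplasty and are grouped by the date it was achieved, so those lost while waiting are missing and the trial can compare only patients who reach surgery

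*Protocol*

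**What the plan says.** Section III.2 of the protocol sets the entry point: "Patients undergoing cranioplasty in our department from 2025 to 2026 due to various reasons leading to decompressive craniectomy will be prospectively collected and analyzed". Overall Design (III.1) sets the comparison: "The trial is organized to compare two distinct patient groups based on the timing of their cranioplasty procedure". On the groups it says "The early group will consist of patients receiving cranioplasty within 6 weeks to 3 months post-decompression" and "the late group will include those undergoing the procedure later than 3 months post-decompression"; the late group has no upper limit.

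Timing is not assigned by the study. Section V states: "As a prospective observational study, it involves no intervention, only prospective data collection". Section IV.1 counts follow-up from the operation: "Follow-up visits will be scheduled at 3 months and 6 months post-cranioplasty until follow-up data collection is completed".

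For bias and confounding, section IV.3 promises that the relevant factors will be built into the plan and the case report forms, and adds: "Statistical methods such as stratified analysis, multivariate analysis, and propensity score will be used to control and correct these factors during data analysis". It names no factor. The Research Background (section I) says that the study is to establish the best time for cranioplasty and so guide treatment. The primary objective (section II) is narrower: neurological outcome of cranioplasty done at different times.

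**The concern.** When to operate is decided for a patient who has had a decompression and is waiting. This design sees that patient only if the operation takes place, and two mechanisms follow.

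- **Loss while waiting.** An early patient has to reach a date between 6 weeks and 3 months. A late patient has to survive and remain a candidate for longer than that. Anyone who drops out of the waiting group by death, deterioration or never being reconstructed is counted nowhere. If waiting does harm by such losses, the harm is invisible and the late group consists of those who came through.
- **Delay caused by complications.** The Risk/Benefit Analysis itself says that infection, hydrocephalus and cerebrospinal fluid leakage become more likely after decompression. Such an event can push surgery past 3 months and also worsen neurological outcome, so late surgery looks worse than it is.

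The first tends to flatter late surgery and the second early surgery. At stake is whether an observed difference, or the lack of one, can be read as an effect of timing.

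**Working it through.** **1. Entry point.** Sample Size (III.1) words it differently: "We aim to enroll a minimum of 500 patients who have undergone decompressive craniectomy". The calendar settles which reading fits. Recruitment ends in January 2026, the last visit is in August 2026, and visits run to 6 months after cranioplasty.

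- Entry at cranioplasty: January 2026 + 6 months = July 2026, inside August 2026.
- Entry at decompression with late surgery: January 2026 + more than 3 months + 6 months = later than October 2026, past the stated end.

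Section VI gives another calendar, with collection to June 2026 and follow-up to December 2026. This also leaves 6 months and also fits entry at surgery.

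**2. Time from decompression to the last visit.** Six weeks is 42/30.4 = 1.4 months. Early: 1.4 + 6 = 7.4 months up to 3 + 6 = 9.0 months. Late: more than 9.0 months, without limit.

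**3. How many could be missing.** The documents give no rate. Assume that a fraction h of waiting patients is lost each month from day 42 (1.38 months). The share lost by month t is 1 − (1 − h)^(t − 1.38).

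- t = 3: h = 0.01 gives 1.6%; h = 0.05 gives 8.0%.
- t = 6: h = 0.01 gives 4.5%; h = 0.05 gives 21.1%.

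**4. What adjustment can and cannot do.** This is an illustrative simulation of 1.5 million patients per scenario; every input is assumed. Half are intended for early surgery. Severity L is standard normal. The probability of a complication is logistic(−1.4 + 0.6L), or 20% at average severity. The probability of a favourable outcome after surgery is logistic(0.2 − 0.6L − 0.8C), where C = 1 with a complication; at average severity this is 55% without and 35% with one. Timing has no effect on outcome after surgery. Loss, where present, strikes only patients on the late path, is likelier with severity and complications, and counts as unfavourable. In C and D an unmeasured frailty factor also raises loss and worsens outcome.

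Differences are early minus late, in percentage points. The first results column compares all patients by intended timing; the others use operated patients only.

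| Scenario | By intended timing, all patients | Crude | Weighted for severity | Weighted for severity and complication |
|---|---|---|---|---|
| A1: half of early-intended patients with a complication delayed, no loss | −0.1 | 4.3 | 2.9 | 0.0 |
| A2: 80% of them delayed, no loss | 0.1 | 7.1 | 4.9 | 0.1 |
| B: no delay, 13.1% of late patients lost | 5.5 | −1.4 | −0.2 | 0.1 |
| C: no delay, 16.2% lost, unmeasured frailty | 4.9 | −4.0 | −2.9 | −2.6 |
| D: half delayed, 17.2% lost, unmeasured frailty | 4.4 | −0.4 | −0.5 | −2.6 |

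The A1 and A2 values in the first column are zero apart from simulation error. As a check on B, 5.5/13.1 = 0.42, so 42% of those lost would have had a favourable outcome, and 13.1% × 0.42 = 5.5 points. Those patients are absent from the operated sample, so no weight within it can recover the 5.5. In C the weighted estimate has the wrong sign, because frail patients were removed from the late group only.

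Scenario A shows the opposite for delay: once the complication is recorded and used, the bias goes.

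**The case against.** The best defence is that the primary objective concerns outcome after cranioplasty. For that question, entry and follow-up start at surgery in both groups, so follow-up contains no immortal time. This stands for the narrower question, but the protocol does not stop there: the Research Background claims the broader one and no limit is stated.

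It can also be said that a complication before surgery is an ordinary confounder, that section IV.3 promises to record confounders, and that the covariate list may sit in a statistical analysis plan not shown here. This stands too. A reader might infer that the planned methods are powerless against complication-driven delay; they are not, provided that the event is captured. What remains is that IV.3 does not say that pre-surgical complications, status or reasons for delay will be captured, and an analysis plan cannot supply data that were never collected.

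A reader might also infer from the Sample Size wording that the 500 include patients who are never operated on. The documents do not support this. Every patient who comes to cranioplasty here has had a decompression, so the two wordings are compatible, and the calendar fits entry at surgery.

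Finally, the magnitudes are assumptions. Delaying 50–80% of early-intended patients with a complication is a strong one, and the crude differences belong to an unadjusted comparison that the protocol does not propose.

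**Conclusion.** The concern holds in a limited form. Entry at surgery and grouping by achieved date mean that patients lost while waiting are missing, and no stratified, multivariate or propensity analysis of the operated patients can recover them. The trial as designed cannot establish the best timing for a patient who is still waiting.

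Delay caused by complications is a second source of bias, removable to the extent that these events and the reason for delay are recorded before surgery and used.

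The direction and size of the net bias cannot be derived from the documents. The figures above show only that the mechanisms can amount to several points and can partly cancel, as in scenario D. A reader might take them as an estimate of this trial's error, or conclude that no useful comparison is possible; neither is supported.

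**What to change.** 1. In sections I and II and in Overall Design, limit the conclusion to patients who reach cranioplasty.
2. Add to the case report form the reason for delay, complications between decompression and cranioplasty, and neurological status just before surgery. Name them as covariates for the propensity score or regression.
3. At each centre, keep a log of candidates at 6 weeks after decompression: planned timing where one exists, and whether the patient was operated on, died or was never reconstructed. Report these losses beside the main result, and repeat the comparison by planned timing as a sensitivity analysis.

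The cost is a log, one form page and a narrower conclusion. No patient's care changes. These items have to be in place during enrolment.

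If the sponsor wants to keep the broader aim, an option is to start the clock at 6 weeks for all candidates and compare timing strategies by clone-censor-weighting. This needs three additions: an outcome at a fixed time from that date for everyone, including patients never operated on (visits are now scheduled only from cranioplasty); an upper limit to the late strategy, set for the analysis only; and longer follow-up than now planned. It is a larger study, not a small amendment.
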